## Abstract

**Background::**

Lumbar radicular pain (LRP) is a common symptom, but a challenging clinical problem. Pulsed radiofrequency (PRF) is a more recently developed technique that uses short pulses of radiofrequency current with intervals of longer pauses to prevent temperature from rising to the level of permanent tissue damage and has been advocated in treatment of such patients. But there were no comparative studies on the analgesic effects according to output voltage during PRF in patients with LRP. The goal of this study is to determine the clinical effect of high-voltage (60V) versus standard-voltage (45V) PRF of lumbar dorsal root ganglion.

**Methods/design::**

This study will be a prospective, double-blind randomized controlled pilot study. In this study, total 20 patients will be recruited and distributed equally into 2 groups: high-voltage (60V) PRF, low-voltage (45V) PRF. Outcomes will be radicular pain intensity; physical functioning; global improvement and satisfaction with treatment; and adverse events. The assessments will be performed at the 3-month follow-up period after the end of the treatments. The findings will be analyzed statistically considering a 5% significance level (*P* ≤ .05).

**Discussion::**

The results of this trial will help determine which voltage could be applied for PRF to dorsal root ganglion in LRP and be a basis for subsequent trials.

## 1. Introduction

Lumbar radicular pain (LRP) is a common symptom, but a challenging clinical problem that involves radiating pain in one or more dermatomes and may be accompanied by chronic nerve irritation and dysfunction.^[1,2]^ Interventional procedures may be considered if conservative treatments, such as physical therapy or medication are initially tried and are not effective.^[2]^

Pulsed radiofrequency (PRF) of interventional procedures is a more recently developed technique that uses short pulses of radiofrequency current with intervals of longer pauses to prevent temperature from rising to the level of permanent tissue damage.^[3,4]^ Although the mechanism of PRF is still not fully understood, PRF is easily accepted as a nerve modulation rather than nerve destruction. Previous studies have shown that this treatment is safe and effective in treating various painful disorders including LRP by intermittently applying high-frequency currents adjacent to the lumbar dorsal root ganglion (DRG).^[5,6]^ However, there have been controversy results about the PRF effect of lumbar DRG.^[7]^ In addition, the effect applied to lumbar DRG did not seem to last longer than PRF applied to other areas.^[8]^

So, subsequent studies should examine whether increasing the dosage and modifying intraoperative parameters of PRF can improve its effects. Luo et al^[9]^ suggested that analgesic efficacy was positively correlated with output voltages during PRF in trigeminal neuralgia. To our knowledge, there has been no comparative study on the analgesic effects according to output voltage during PRF in patients with LRP. Thus, in this study, we will aim to assess the clinical effects of high-voltage (60V) versus low-voltage (45V) PRF of the lumbar DRG.

## 2. Materials and methods

### 2.1. Trial registration

This trial has received complete ethical approval from the Ethics Committee of Catholic Kwandong University International St. Mary’s Hospital (IS22OISE0032). This trial was registered at the Clinical Trial Registry of Korea (CRIS, www.cris.nih.go.kr.) (Registration number KCT0007578).

### 2.2. Trial design

As a part of the ethical approval process, we will provide a written informed consent form to the participants before their enrollment in the study. This study will be a double blind, randomized controlled trial to compare the 2 groups (1:1). This study will be performed in 20 participants with LRP and conducted on outpatients visiting the pain clinic of International St. Mary’s Hospital, Catholic Kwandong University. The clinical trial and the items to be examined in this study are presented in Figure 1.

**Figure 1. F1:**
[figure not shown]
Flowchart of study design. PRF = pulsed radiofrequency treatment.

### 2.3. Inclusion criteria

Age ≥20 years oldPain intensity ≥5 out of 11 on the numerical rating scale (NRS)Chronic LRP lasting ≥12 weeksPrevious failure of conservative management such as physiotherapy, exercise therapy, or analgesic medicationsLumbar spinal stenosis confirmed by magnetic resonance imagingPatients who received conventional fluoroscopy-guided diagnostic/therapeutic transforaminal epidural injections with local anesthetics and steroidsPatients who reported persistent pain (NRS score ≥5) after receiving TFESIPatients who received at least 2 epidural steroid injections in the 3 months preceding PRF treatment

### 2.4. Exclusion criteria

Patient refusalAge <20 yearsUnbearable pain >9–points on NRS, pain <4–points on NRSAcute pain of onset lasting <12 weeksSigns of progressive motor weakness or neurologic deficitsAllergies to steroids or contrast dyesCoagulopathyEpidural steroid injection within the previous 4 weeksSystemic infection, injection site infectionMalignancy

### 2.5. Assignment of interventions and blinding

Participants will be randomized using a computer-generated scheme to either treatment group: low-voltage group and high-voltage group. Immediately prior to the procedure, procedure-performing physician ([name]) will open a sequentially numbered opaque envelope with group assignment listed inside. All participants will remain blind to the group assignment before, during, and after the PRF and all efforts will be made to provide identical treatment experiences. The injection procedure and type of drug used for treatment will be not revealed to the patients until study completion. The researcher who gathered post-procedure data also will be blind to group assignment.

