### 2.6. Procedures

All procedure will be performed under fluoroscopic guidance. A single fluoroscopy C-arm system will be used. The patient will be placed in the prone position with a pillow under the lower abdomen. After sterile preparation of the needle insertion area, the skin will be infiltrated with 1% lidocaine, and a 22-guage, 4-in RF cannula with a 10 mm curved active tip will be advanced under fluoroscopic guidance. After appropriate positioning of the RF cannula, the stylet will be replaced by the RF probe and the probe will be connected to the PRF generator (Radiofrequency Ablation for Pain Management, G4™ RF Generator; Cosman Medical, Burlington, NJ). The final definite position of the RF probe will require a sensory stimulation (50 Hz) threshold ≤0.4 V, which create paresthesia corresponding to the existing distribution of the patient’s radicular pain. The motor stimulation threshold (2 Hz) should be more than 1.5 times greater than the sensory stimulation threshold, and impedance <400 Ω is also required. The position of the RF cannula will be slightly adjusted after each cycle of treatment, and the motor/sensory stimulation will be also performed at the same time for confirmation.

In experimental high-voltage group, the output voltage will be set to 60V with temperature no more than 42°C, pulsed width of 20 millisecond, frequency at 2 Hz, and duration for 120 seconds and 3 cycles of PRF will be applied. In low-voltage group, only the output voltage will be different to 45V compared to experimental group.

The generator will be manipulated by the operating room nurse, and the display will be concealed from the patient and the procedure-performing physician. After PRF, the needle will be further retreated and then repositioned at the safe triangle. After confirmation of epidural spread using a contrast dye, 1 mL of 0.3% mepivacaine will be injected.

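### The operator opens the allocation envelope (2.5), so hiding the generator display from the operator (2.6) cannot blind the operator; the two sections must be reconciled

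*Protocol article*

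**What the plan says.** On allocation, section 2.5 states that the "procedure-performing physician ([name]) will open a sequentially numbered opaque envelope with group assignment listed inside", and that this happens immediately before the procedure. The same section names two blinded parties. For patients: "All participants will remain blind to the group assignment before, during, and after the PRF". For the person collecting outcomes: "The researcher who gathered post-procedure data also will be blind to group assignment". It makes no statement that the physician is blind.

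On the conduct of the procedure, section 2.6 states: "The generator will be manipulated by the operating room nurse, and the display will be concealed from the patient and the procedure-performing physician". It also fixes the contrast between the arms: "In low-voltage group, only the output voltage will be different to 45V compared to experimental group".

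The abstract describes a "prospective, double-blind randomized controlled pilot study" in which "total 20 patients will be recruited and distributed equally into 2 groups". Section 2.2 also calls the trial double blind.

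**The concern.** Hiding the display from the physician has no evident purpose other than to keep the physician unaware of the arm. Section 2.5 gives that physician the same information shortly beforehand. The nurse, who must know the voltage in order to set it, is not the person who opens the envelope.

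What is at stake is performance bias. The operator judges the position of the probe, adjusts the cannula after each cycle and repeats the stimulation test. The patient has to report whether the paresthesia matches the radicular pain, so operator and patient communicate during treatment. Both primary outcomes in section 2.7, NRS and ODI, are reported by the patient. Knowledge of the arm could affect the care taken over placement, or reach the patient through what the operator says or does. A blinded outcome researcher cannot remove bias that has entered by either route.

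**Working it through.** The plan gives no figure to reproduce on this point. The check is a comparison of the two sections.

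1. **Who learns the assignment, and when (2.5).** The physician who performs the procedure opens the envelope, and the group is listed inside. The groups are the low-voltage and the high-voltage group.

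2. **What the concealed display would reveal (2.6).** Output voltage is the only planned difference between the arms, 60 V against 45 V. To know the group is to know the voltage.

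3. **Consequence for the operator.** Steps 1 and 2 together mean that the display holds nothing about the arm that the operator has not already read. Concealing it from the operator therefore cannot blind the operator.

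4. **Consequence for the patient.** The patient does not open the envelope. Concealing the display from the patient still withholds the voltage and still protects the patient's blinding.

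5. **Consequence for the outcome researcher.** Nothing in 2.5 or 2.6 gives this person the assignment, so the stated blinding stands.

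6. **Extent.** One envelope is opened before each procedure and 20 patients are planned, 10 per group (20 / 2). The operator is unblinded in 20 of 20 procedures.

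7. **Room for operator judgement (2.6).** The final position must meet limits that are the same in both arms: sensory threshold at most 0.4 V, motor threshold more than 1.5 times the sensory threshold, impedance below 400 Ω. These are bounds and not single values, so more than one position can satisfy them. The position is then slightly adjusted after each cycle. Knowledge of the arm can act within those bounds.

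8. **Size of the bias.** The document gives nothing from which the effect of operator knowledge on NRS or ODI could be estimated, so no range is offered.

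**The case against.** The strongest reply is that the blinding the trial promises is intact. Section 2.5 names the patient and the outcome researcher as blind and never the physician, and a double-blind label can be met by those two parties. Patients are to be given identical treatment experiences as far as possible. Placement is held to numerical limits common to both arms. Section 2.7 records stimulation voltages, impedance and procedure duration, so a difference between arms in placement could be looked for afterwards. An operator who is not blinded may also be acceptable in a 20-patient pilot of a procedure.

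Much of this stands, and it rules out four stronger readings that a reader might infer:

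- *That concealing the display is pointless.* It is ineffective for the operator only. For the patient it works, and that matters because the primary outcomes are patient-reported.
- *That the double-blind label is false.* The label is compatible with a blinded patient and a blinded outcome researcher, both of which 2.5 states.
- *That allocation concealment is broken.* Sequentially numbered opaque envelopes opened just before treatment do conceal the allocation at enrolment.
- *That 20 patients × 3 cycles = 60 cycles measures the damage.* That product counts exposure and not bias, and outcomes are measured per patient.

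The reply does not explain why 2.6 hides the display from the physician. If the operator is meant to be unblinded, that part of 2.6 serves no purpose. If the operator is meant to be blind, 2.5 defeats it. Nor do the numerical limits and recorded settings exclude verbal cues or differences in effort within the limits.

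**Conclusion.** The two sections are inconsistent, and the point holds for the operator. As written, the operator knows the arm in all 20 patients, and concealing the display from the operator is ineffective. The blinding of the patient and of the outcome researcher is not itself contradicted.

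The consequence is a possible performance bias on NRS and ODI, of unknown size and not demonstrated. It cannot be removed in the analysis once patients have been treated, so the text should be settled before the first procedure.

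The conclusion rests on two readings of the text: that the physician reads the assignment in the envelope, and that it identifies the group as low or high voltage. Section 2.5 supports both, and the article mentions no coded label that would keep the voltage from the physician.

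**What to change.** **Preferred.** Change 2.5 so that the operating room nurse who sets the generator opens the envelope out of sight of the physician and the patient, sets the assigned voltage, and keeps the assignment from the physician, the patient and the outcome researcher until study completion. Section 2.6 can then stay as it is, and 2.5 can add the physician to those who are blind.

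**If that is not feasible.** Reconcile the sections by stating in both that the operator is unblinded and that only the patient and the outcome researcher are blind, and remove from 2.6 the concealment of the display from the physician. This makes the text consistent but leaves the route to performance bias open, which the report should acknowledge.

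**Cost.** One sentence in 2.5 and a short instruction to the nurse, with no extra visits or patients. No extra staff should be needed, because 2.6 already has the nurse operating a concealed generator. That assumes the nurse takes no part in recruiting patients or collecting outcomes, which the article does not state and the sponsor should confirm.

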### 2.6. Procedures

All procedure will be performed under fluoroscopic guidance. A single fluoroscopy C-arm system will be used. The patient will be placed in the prone position with a pillow under the lower abdomen. After sterile preparation of the needle insertion area, the skin will be infiltrated with 1% lidocaine, and a 22-guage, 4-in RF cannula with a 10 mm curved active tip will be advanced under fluoroscopic guidance. After appropriate positioning of the RF cannula, the stylet will be replaced by the RF probe and the probe will be connected to the PRF generator (Radiofrequency Ablation for Pain Management, G4™ RF Generator; Cosman Medical, Burlington, NJ). The final definite position of the RF probe will require a sensory stimulation (50 Hz) threshold ≤0.4 V, which create paresthesia corresponding to the existing distribution of the patient’s radicular pain. The motor stimulation threshold (2 Hz) should be more than 1.5 times greater than the sensory stimulation threshold, and impedance <400 Ω is also required. The position of the RF cannula will be slightly adjusted after each cycle of treatment, and the motor/sensory stimulation will be also performed at the same time for confirmation.

In experimental high-voltage group, the output voltage will be set to 60V with temperature no more than 42°C, pulsed width of 20 millisecond, frequency at 2 Hz, and duration for 120 seconds and 3 cycles of PRF will be applied. In low-voltage group, only the output voltage will be different to 45V compared to experimental group.

The generator will be manipulated by the operating room nurse, and the display will be concealed from the patient and the procedure-performing physician. After PRF, the needle will be further retreated and then repositioned at the safe triangle. After confirmation of epidural spread using a contrast dye, 1 mL of 0.3% mepivacaine will be injected.

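### The operator reads the allocation before placing the probe, although the arms differ only in a voltage applied later and the protocol hides that voltage from the same operator

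*Protocol article*

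**What the plan says.** Protocol article, section 2.5, fixes who learns the group and when: "Immediately prior to the procedure, procedure-performing physician" is the person who "will open a sequentially numbered opaque envelope with group assignment listed inside". Participants and the researcher who collects the post-procedure data are named as blind; the operator is not named either way.

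Section 2.6 describes what follows. The cannula is advanced, the probe is connected, and the position is tested: "The final definite position of the RF probe will require a sensory stimulation (50 Hz) threshold ≤0.4 V", with paresthesia matching the patient's own pain. The motor threshold "should be more than 1.5 times greater than the sensory stimulation threshold, and impedance <400 Ω is also required". The arms then differ in output voltage alone, 60 V or 45 V, over three cycles. Placement is not a single event: "The position of the RF cannula will be slightly adjusted after each cycle of treatment", and stimulation is repeated at that point. The operating room nurse works the generator, and "the display will be concealed from the patient and the procedure-performing physician".

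Section 2.8 analyses every randomised subject and counts loss to follow-up or withdrawal as treatment failure. It does not mention patients in whom the position requirements are not met.

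**The concern.** Nothing that the operator does up to acceptance of the first position depends on the arm, so there is no reason for the operator to know it. Yet the operator does know it, and has discretion: how long to search, whether the reported paresthesia matches the pain closely enough, which of several acceptable positions to settle on, and whether to give up. If that discretion is used differently by arm, the groups differ in electrode placement as well as in voltage, and the analysis cannot separate the two.

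The same early opening means that a patient in whom no acceptable position was found would already be randomised. Such a patient would say nothing about 60 V against 45 V, but would count as one of ten in an arm.

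**Working it through.** **1. Order of steps, sections 2.5 and 2.6 side by side**

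| Step | Source | Does it need the allocation? |
|---|---|---|
| Physician opens the envelope | 2.5, just before the procedure | – |
| Cannula advanced, probe connected | 2.6 | No |
| Sensory, motor and impedance requirements tested | 2.6 | No, identical in both arms |
| Output voltage applied, cycle 1 | 2.6, nurse at the generator | Yes, nurse only |
| Cannula adjusted and stimulation repeated after each cycle | 2.6 | No |

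The only person who needs the allocation is the nurse, and only from the fourth row on. As written, the physician has it from the first row.

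**2. The two sections against each other.** Concealing the display from the physician can only serve to keep the voltage unknown to that physician. Once the physician has read the envelope, the concealment achieves nothing. Both provisions cannot be doing their job.

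**3. Size of the positioning-failure part.** There is no figure in the plan to reproduce: the 20 patients are given without effect size, standard deviation or power.

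Inputs: 20 patients allocated 1:1 (abstract and section 2.2), so 10 per arm; every randomised subject analysed (section 2.8). Assumptions: a patient who cannot be positioned receives neither voltage, and such failure is equally likely in both arms. Let H and L be the mean improvement at 60 V and 45 V, U the mean for a patient without PRF (or whatever failure score is given in both arms), and D = H − L.

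- One failure in the 60 V arm: 0.9H + 0.1U − L = D − 0.1(H − U).
- One failure in the 45 V arm: H − 0.9L − 0.1U = D + 0.1(L − U).
- Average of the two: D − 0.05(H − L) = 0.95D, a shrinkage of 1/20 = 5%.
- Two failures, on average: (1 − 2/20)D = 0.90D.

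The failure rate p is not given. Over an assumed range, the chance of at least one failure is 1 − (1 − p)^20, and the expected shrinkage is 20p × 5%:

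| p (assumed) | Expected failures among 20 | Chance of at least one | Expected shrinkage |
|---|---|---|---|
| 0% | 0 | 0% | 0% |
| 2% | 0.4 | 33% | 2% |
| 5% | 1 | 64% | 5% |
| 10% | 2 | 88% | 10% |

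**The case against.** The best case for the plan has several parts.

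- *The thresholds define when positioning is complete; they are not a pass/fail screen.* This stands. No text says that a patient can fail them or then goes untreated. The dilution figures are conditional, and at a rate of zero that part of the point vanishes.
- *Timing alone does not bias the comparison.* This stands too. The requirements are the same in both arms and are tested before the voltages differ. Bias needs an operator who behaves differently by arm, which is possible but not shown.
- *A reader might infer that each failure removes 10% of an arm.* The documents do not support this. Section 2.8 keeps every randomised subject, so nobody is removed, and a power calculation with 9 or 8 per arm would model something the plan rules out. Nor does every failure shrink the contrast: if PRF works at both voltages, a failure in the 45 V arm widens it. The 5% is an average over arms.
- *A reader might infer that the double-blind label is false.* That goes too far. Section 2.5 blinds the participants and the researcher who gathers post-procedure data, and that may be all the label means.
- *Placement differences can be seen afterwards.* Section 2.7 does record stimulation voltages, impedance and procedure duration. With 10 per arm, such a check could detect only large differences, and it would not undo them.
- *Handling of technical failures may sit in a fuller document.* Agreed, and its absence is not the point. The article does fix who opens the envelope and when, and that choice conflicts with its own concealment of the display.

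**Conclusion.** The point holds as a conflict between sections 2.5 and 2.6 that leaves the operator aware of the arm at the first placement and at each repositioning. This follows from the text and rests on no assumed rate. How much bias results cannot be calculated from the document.

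The positioning-failure part is secondary. It amounts to an average shrinkage of the expected difference of about 5% per affected patient, with nobody removed from the analysis. It assumes that such failures occur, which the document neither states nor excludes, and that they are unrelated to arm. The change is worth making before enrolment because it is simple and costs almost nothing.

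**What to change.** Reconcile sections 2.5 and 2.6 as follows.

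- The operating room nurse who sets the generator opens the next numbered envelope only after the first probe position has met the requirements already stated in 2.6, and does not show it to the physician.
- A patient who cannot be positioned is not randomised; the unopened envelope goes to the next patient.
- A patient whose position fails at re-testing after a cycle has already been randomised and stays in the intention-to-treat set in the allocated arm.

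Moving the opening time without changing who opens the envelope would not be enough, because the later repositionings would still be made by someone who knows the arm.

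Cost: about one sentence in 2.5, plus a line for failures after a cycle. No staff are added, no threshold or procedural step changes, and nobody new learns the allocation, since the nurse sets the voltage anyway. The small downside is that the comparison then applies to patients in whom the probe can be positioned.
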